### 2.2. Setting and Geographic Clusters

The bundle implementation will be conducted in nine public health facilities in Sierra Leone: eight in the Greater Freetown area and one in the city of Bo, including one tertiary hospital, four secondary hospitals, and four community health centers (CHCs), as described below and in Table 1.

Participating facilities:Tertiary: Princess Christian Maternity Hospital (PCMH)—Freetown.Secondary: Bo Government Hospital, Rokupa Government Hospital, King Harman Road Government Hospital, and Waterloo CHC (functioning as a secondary hospital).Primary (CHCs): Jenner Wright, Kissy, Ross Road, St. Anthony’s (Note: These CHCs do not perform cesarean sections or care for small/sick newborns.).

### 2.3. Implementation (The Service Delivery Bundle)

The service delivery bundle comprises a newborn package and a maternal package, supported by cross-cutting implementation strategies.

Newborn Care PackageCurriculum: Implementation of the World Health Organization Essential Newborn Care Course (ENCC) Parts 1 and 2.Respiratory Support: Training and deployment of Vayu bCPAP systems and Vayu oxygen blenders to prevent hyperoxic lung injury and retinopathy of prematurity.Equipment: Provision of bag-and-mask devices, suction units, heart rate monitors, and pulse oximeters, in addition to Vayu bCPAP systems, oxygen blenders, and consumables.Kangaroo Mother Care (KMC): Expansion of KMC, to ensure neonatal euthermia, for the immediate care of small and sick newborns.Maternal Care PackagePPH Management: Implementation of the WHO Postpartum Hemorrhage Package, including blood-loss quantification aids, intrauterine balloons, and anti-shock garments.Advanced Diagnostic Equipment: Training and deployment of Butterfly iQ3 handheld ultrasound probes (POCUS) for delivery wards and point-of-care hemoglobin testing.Risk Stratification: Enhanced triage and risk assessment using handheld ultrasound, improved use of fetal Dopplers and sphygmomanometers, and hemoglobin testing.Cross-cutting StrategiesRespectful Care: Principles and practices of respectful care will be integrated into clinical training and mentoring activities.Infection Control and Prevention (IPC) Supplies: Refresher training and supplies to improve water, sanitation, and hygiene practices.Service Optimization: Facility-based teams will identify unique challenges and implement and document improved practices.Implementation StrategyMentorship: Project HOPE will supply external mentors to cascade training and provide supportive supervision while observing patient care practices.Champions: Two internal “Champions” will be recruited at each facility to support training scale-up and practice.Practice Corners: Establishment of LDHF practice stations for skills retention.Ancillary Services, Equipment, and SuppliesData: Mentoring healthcare staff with documentation challenges and collecting and cleaning data.Equipment: Ancillary equipment includes Dopplers, stethoscopes, pulse oximeters, sphygmomanometers, thermometers, glucometers, oxygen concentrators, heart rate monitors, resuscitation equipment, and training simulators.Supplies: Consumables for bCPAP, hemoglobin, and urine testing, WASH equipment and supplies, personal protective equipment and sanitation supplies, hemorrhage kits and commodities, and printed materials.

### 2.4. Study Outcomes

To align with the Hybrid Type 1 effectiveness-implementation framework, the review metrics are strictly delineated into clinical effectiveness outcomes (measuring the health impact on mothers and newborns) and implementation outcomes (measuring the operational success, fidelity, and sustainability of the service delivery bundle).

#### 2.4.1. Clinical Effectiveness Outcomes

The primary clinical outcomes focus on immediate survival and severe morbidity:Primary Neonatal: Reduction in the neonatal mortality rate within the first 24 h.Primary Maternal: Reduction in the incidence of postpartum hemorrhage (≥500 mL).Secondary Outcomes: Fresh stillbirth rate, institutional maternal case fatality rate, neonatal transfer rate for advanced care, and survival rate of sick newborns admitted to the SCBU.

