### 1.2. Strategic Alignment and Policy Context

The bundle operationalizes two national frameworks, including the Sierra Leone National Health Sector Strategic Plan 2021–2025 and the Ministry of Health and Sanitation (MoHS) Child Survival Action Plan 2023–2025, both of which prioritize reductions in under-five and maternal mortality through strengthened newborn services [24,25]. The MoHS has established special care baby units in 16 districts and scaled up Helping Babies Breathe nationally [26]. Two implementation gaps remain. First, the more comprehensive WHO Essential Newborn Care Course (ENCC), particularly Part 2, covering the first 24 h of life has not been introduced [27]. Second, the WHO Postpartum Hemorrhage Package has not been operationalized as an integrated bundle linking blood-loss quantification, intrauterine balloon tamponade, and active management of the third stage of labor. This protocol addresses both gaps; Figure 1 maps each bundle component to its corresponding national policy objective.

The maternal component aligns with both the national plan and global best practices by implementing the WHO Postpartum Hemorrhage Package and transitioning care from simple management to a comprehensive PPH “bundle” approach. Innovative maternal triage and risk assessment strategies address potential upstream sources of intrapartum complications. Aligned with these national priorities, the primary objective of implementing this targeted bundle is to improve maternal and newborn outcomes. Figure 1 shows the alignment of the maternal and newborn bundle with national goals.

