### 1.3. Implementation Logic Model

The implementation logic follows a pathway in which resource inputs lead to enhanced clinical capacity and improved outcomes.

Inputs: Newborn: Vayu bCPAP, oxygen blenders, resuscitation equipment, monitors, oxygen concentrators, and consumables. Maternal: hemorrhage quantification and treatment tools, Butterfly ultrasound, Hemocue, heart tone Dopplers, and consumables.Activities: Training in ENCC Parts 1 and 2, Vayu bCPAP training, WHO PPH Course, and basic ultrasound diagnosis training; establishment of facility-based “Champions” and LDHF practice corners. Monthly mentoring, supportive supervision, and scale-up assistance.Outputs: We anticipate timely resuscitation (within one minute) and improved treatment of respiratory distress, in addition to improved maternal risk stratification and management of PPH.Outcomes: We anticipate a reduction in perinatal mortality, improved SCBU neonatal survival, and decreases in PPH incidence, institutional maternal mortality, and morbidity.Impact: We anticipate a sustained reduction in maternal and neonatal mortality and morbidity, contributing to SDG targets.

This implementation logic model is based on the following assumptions:There will be sustained political support for this project.Supply chain systems will ensure maternal and newborn commodity security across supported facilities.Staff will remain committed to project implementation.

The main components of the project plan, as outlined above, are shown in Figure 2.

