### 1.4. Objectives

The primary objective of implementing a targeted service delivery bundle is to enhance maternal and newborn outcomes in a cohort of nine hospitals over a three-year period. These service delivery improvements aim to achieve the following:Reduce neonatal mortality: Achieve a 50% reduction in neonatal deaths within the first 24 h and a 10% reduction in intrapartum or “fresh” stillbirths compared to a baseline assessment.Reduce neonatal morbidity: Achieve a 25% reduction in neonatal transfers to advanced care.Improve neonatal clinical practice: Ensure that 80% of SCBU admissions with respiratory distress receive appropriate oxygen therapy.Reduce maternal morbidity: Achieve a 40% reduction in the incidence of postpartum hemorrhage and a 50% reduction in institutional maternal mortality.Improve obstetric clinical practice: Ensure that 90% of deliveries utilize active management of the third stage of labor with uterotonics to prevent hemorrhage.Strengthening diagnostic capacity: Deploy handheld ultrasound and point-of-care hemoglobin testing to improve obstetric risk stratification.Maintain competency: Implement a “train-the-trainer” model, mentoring, low-dose high-frequency practice, and supportive supervision to maintain high performance on knowledge and skills checks at 12-month intervals.

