## 2. Materials and Methods

### 2.1. Implementation Design and Timeline

The longitudinal review of this protocol will utilize a Hybrid Type 1 effectiveness-implementation design. This approach allows for the primary review of the clinical effectiveness of the maternal and newborn bundle on patient outcomes, while simultaneously observing and gathering data on its feasibility, acceptability, and sustainability within the targeted facilities. The review employs a prospective, quasi-experimental before-and-after design.

Routinely collected service-delivery data from the three months immediately before implementation will be compared with data from the final three months of the 36-month implementation period, with continuous monitoring throughout. This design was selected for three reasons. First, the bundle is delivered as a facility-level package of training, equipment, mentoring, and supervision; patient-level randomization would not preserve intervention integrity. Second, withholding the bundle from comparable facilities is ethically difficult given Sierra Leone’s mortality burden and the established effectiveness of each component. Third, all participating facilities report to the national District Health Information System 2 (DHIS2), providing a long retrospective time-series that strengthens within-facility comparisons. Limitations arising from the absence of concurrent control are discussed in Section 3.5. Implementation will be divided into three phases:Preparatory Phase: Baseline analysis and equipment procurement. Based on these findings, a causal/bottleneck analysis of the adequacy of perinatal care quality will be conducted and shared with hospital administrations, and mitigation plans will be prepared.Implementation Phase (months 1–18): Training of trainers and equipment deployment. Training scale-up, mentoring, and supportive supervision, to include midwives, nurses, surgical and community health officers, and physicians (2024–2025).Sustainability Phase (months 19–36): Continue supportive supervision and transition to MoHS ownership (2026–2027).

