**Figure 2 mps-09-00096-f002:**
[figure not shown]
Implementation logic model.

**Table 1 mps-09-00096-t001:** Baseline characteristics and target training populations of participating healthcare facilities (2023).

Facility Name	Location (City)	Number of Annual Births	Maternal Deaths (2023)	Neonatal Deaths (2023)	Number of Annual C/S	Healthcare Workers Trained in Past 2 Years	Total Healthcare Workers to Be Trained
Bo Government Hospital	Bo	3226	34	191	1053	28	23
Jenner Wright Clinic	Freetown	412	17	6	14	13	-
King Harman Road Government Hospital	Freetown	712	8	15	331	9	87
Kissy CHC	Freetown	440	17	4	3	19	-
Princess Christian Maternity Hospital	Freetown	7099	63	464	3016	12	125
Rokupa Government Hospital	Freetown	1495	1	54	599	5	65
Ross Road CHC	Freetown	626	3	1	3	29	-
St. Anthony’s CHC	Freetown	511	19	2	5	27	-
Waterloo CHC	Waterloo	1015	17	11	20	8	23

**Table 2 mps-09-00096-t002:** Education and training.

Category	Indicator	Definition
Training uptake	Number of healthcare workers trained	Total number of midwives, nurses, physicians, and other staff completing WHO ENCC and PPH training modules
	Training completion against targets	Number completing training/facility training target
Skills retention	Frequency of LDHF practice sessions	Number of documented low-dose, high-frequency practice sessions per facility
	OSCE performance scores	Percentage of participants achieving competency on Objective Structured Clinical Examinations (OSCEs)
	Skills retention at 12 months	Percentage of trained staff maintaining competency at 12-month reassessment
Mentorship and supervision	Mentorship visits completed	Number of supportive supervision and mentorship visits conducted per facility
	Practice corner utilization	Frequency of use of facility-based LDHF practice stations

**Table 3 mps-09-00096-t003:** Maternal and newborn measures with definitions.

Category	Indicator	Definition
Maternal indicators	PPH incidence (500 cc)	[# of PPH incidence (500 cc)]/[total births]
	Uterotonics used for PPH prevention	[# of uterotonics used for PPH prevention]/[total births]
	Direct obstetric case fatalities	[# maternal deaths]/[# of total births]
	Admission triage scans	[# of ultrasound scans]/[# of maternal admissions]
	Abnormal scan findings	[# of abnormal scans]/[# of scans]
Neonatal indicators	Fresh stillbirths	[# of fresh stillbirths]/[total births]
	Neonatal case fatality rate < 24 h	[# of neonatal deaths < 24 h]/[total births]

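### The PPH ≥500 mL primary outcome is compared across a change in blood-loss measurement that the bundle itself makes, so the recorded change mixes detection with effect

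*Protocol article*

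**What the plan says.** - **Outcome.** Section 2.4.1 of the protocol article names "Primary Maternal: Reduction in the incidence of postpartum hemorrhage (≥500 mL") as the primary maternal outcome. Section 2.5 lists PPH incidence among four primary outcomes. Table 3 defines it as the number "of PPH incidence (500 cc)]/[total births" and gives no method of measurement for either period.
- **Target.** Section 1.4: "Achieve a 40% reduction in the incidence of postpartum hemorrhage and a 50% reduction in institutional maternal mortality".
- **Measuring tools.** Section 2.3 describes the maternal package as "Implementation of the WHO Postpartum Hemorrhage Package, including blood-loss quantification aids, intrauterine balloons, and anti-shock garments". Section 1.3 lists among project inputs "Maternal: hemorrhage quantification and treatment tools, Butterfly ultrasound, Hemocue, heart tone Dopplers, and consumables". Section 2.3 also has project staff mentoring facilities on documentation.
- **Before the project.** Section 1.2 says that "the WHO Postpartum Hemorrhage Package has not been operationalized as an integrated bundle linking blood-loss quantification, intrauterine balloon tamponade" and the other elements.
- **Comparison.** Section 2.1: "Routinely collected service-delivery data from the three months immediately before implementation will be compared with data from the final three months" of the 36-month period. Section 2.6 calls the baseline retrospective. Section 2.7 names ANOVA, t-tests and chi-square tests.
- **Limitations.** Section 3.5 acknowledges that there is no control group and that the baseline depends on the quality of old registers, to be mitigated by cleaning and cross-verification. It does not mention a change in how PPH is detected.
- **Maternal mortality.** Section 2.5 makes institutional maternal mortality primary. Section 2.4.1 lists an institutional maternal case fatality rate as secondary.

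**The concern.** A case counts as PPH only if someone judges that at least 500 mL was lost and writes it down. The intervention changes both steps: it supplies quantification aids, trains staff to recognise PPH and mentors them in documentation. The baseline window lies wholly before these changes and the final window wholly after them. With no concurrent control, nothing in the comparison separates better counting from fewer haemorrhages.

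A statistical analysis plan cannot repair this later. The retrospective baseline is fixed by the design, and no cleaning or modelling recovers blood loss that was not measured at the time. What is at stake is the reading of the maternal primary result and of the 40% target: a real benefit could look smaller than it is, absent, or in an extreme case reversed.

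**Working it through.** The plan gives no baseline PPH rate, sample size, power or alpha, so there is no figure of its own to reproduce.

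**Model.** Let s0 and s1 be the shares of true PPH cases recorded at baseline and in the final window, ignoring false positives. Then:

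recorded ratio = true ratio × (s1/s0)

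The true ratio at target is 1 − 0.40 = 0.60 (section 1.4). All values of s0 and s1 below are assumptions; the documents give none.

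| s0 | s1 | s1/s0 | Recorded change, true 40% fall (0.60 × s1/s0 − 1) | Recorded change, no true effect (s1/s0 − 1) |
|---|---|---|---|---|
| 0.90 | 0.90 | 1.00 | −40% | 0% |
| 0.80 | 0.90 | 1.125 | −32.5% | +12.5% |
| 0.70 | 0.90 | 1.29 | −23% | +29% |
| 0.60 | 0.90 | 1.50 | −10% | +50% |
| 0.50 | 0.90 | 1.80 | +8% | +80% |
| 0.50 | 0.95 | 1.90 | +14% | +90% |

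**Break-even.** The recorded change is zero when s1/s0 = 1/(true ratio). For a true 40% fall this is 1/0.60 = 1.67. For true falls of 30%, 20% and 10% it is 1.43, 1.25 and 1.11, so a smaller benefit is masked by a smaller shift in detection.

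**Opposite direction.** If s is read as recorded over true cases, over-recording at baseline makes s1/s0 less than 1. A recorded 40% fall with no true effect would then need s1/s0 = 0.60.

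**Precision does not protect.** The nine rows of Table 1 sum to 15,536 births a year, so about 15,536/4 = 3,884 per three-month window. The calculations below assume two-sided alpha 0.05 and ignore clustering by facility.
- Same detection in both windows, 40% fall: power is above 0.99 at an assumed recorded baseline rate of 5%, 10% or 15%. Sample size is not the obstacle.
- No true effect, assumed true rate 10%, s0 = 0.70 and s1 = 0.90: recorded rates are 7% and 9%, and a chi-square test would call this false rise significant with probability about 0.90.

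**Institutional maternal mortality as the main maternal evidence.** Table 1 gives 34 + 17 + 8 + 17 + 63 + 1 + 3 + 19 + 17 = 179 maternal deaths; 179/15,536 = 1.15%, or about 45 per window. The 50% target means 0.58% in the final window, a difference of 0.576 percentage points with a standard error of about 0.210. Then 0.576/0.210 = 2.74, and 2.74 − 1.96 = 0.78, which gives power of about 0.78. For a 40% or 30% fall it is about 0.57 or 0.34.

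The Table 1 counts need checking first. The four primary CHCs report 17 + 17 + 3 + 19 = 56 deaths in 412 + 440 + 626 + 511 = 1,989 births (2.8%), against 63 in 7,099 (0.9%) at the tertiary hospital.

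**The case against.** The strongest reply is that lower baseline detection is inferred. Section 1.2 says that the linked package was not in operation; it does not say that blood loss went unmeasured. **This stands:** the size of the bias is unknown, and its direction is likely rather than established.

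A second reply is that moderate improvements in detection only dilute the effect. If detection improved, a recorded fall would be a conservative estimate and still informative. **This stands too,** but only on the condition that detection improved, which the plan gives no means of verifying.

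Three stronger readings may tempt a reader, and the documents do not support them:
- *The 40% target is bound to be missed.* That follows only if s1 > s0 is assumed from the outset.
- *PPH incidence is the wrong outcome because the bundle treats haemorrhage only after 500 mL is lost.* Balloons and anti-shock garments do act late, but section 1.4 also aims for uterotonic prophylaxis in 90% of deliveries, which can lower incidence.
- *Maternal death is free of the problem.* It does not depend on estimating blood loss, but documentation mentoring may change how completely deaths are recorded.

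Finally, section 3.5 does raise register quality. **This does not answer the point:** cross-verification can correct entries, but it cannot supply a measurement that was not made, and the section does not say that the intervention itself changes ascertainment.

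**Conclusion.** The concern holds. As planned, the primary PPH comparison estimates the true change multiplied by s1/s0, and nothing in the design separates the two factors. That much rests on the documents alone.

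The size rests on assumed sensitivities. A modest gain in detection (0.80 to 0.90) turns a true 40% fall into a recorded fall of 32.5%. A recorded rise needs a more than 1.67-fold gain, so it is possible but not the expected result. If old registers over-recorded PPH, the bias favours the bundle. In either case the recorded change cannot serve as the test of the maternal effect or of the 40% target. The outcome remains useful as description and within a period of constant measurement.

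**What to change.** 1. **Sections 2.4.1, 2.5 and 2.7:** report the pre-implementation versus final-period PPH comparison as descriptive, not as the test of the maternal effect or of the 40% target.
2. **Section 2.7:** add a PPH analysis restricted, at each facility, to months in which quantification was in use. State that its early months are already partly treated, so it may understate the benefit.
3. **Section 2.7:** show the PPH change implied over a stated range of s1/s0, including values below 1.
4. **Section 3.5:** name the change in ascertainment caused by the intervention as a limitation.
5. **Sections 2.4.1 and 2.5:** reconcile whether institutional maternal mortality is primary, and rest the maternal conclusion mainly on it. State that its recording may also change, that the CHC death counts in Table 1 need checking, and that power is about 0.78 for the 50% target under the assumptions above.

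**Cost.** Mostly wording, plus a recorded start date of quantification and monthly PPH counts for each facility. The real downside is that the 40% PPH target can no longer be claimed against the historical registers.

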#### 2.4.2. Implementation Outcomes

Implementation success will be evaluated through metrics of fidelity, uptake, and sustainability:Fidelity and Adherence: The proportion of eligible SCBU admissions successfully initiated on Vayu bCPAP; the proportion of deliveries utilizing active management of the third stage of labor (AMTSL) with uterotonics; and the proportion of obstetric admissions receiving triage ultrasound scans.Uptake and Penetration: The total number of healthcare workers (midwives, nurses, physicians) successfully completing the WHO ENCC and PPH training modules against facility targets.Sustainability and Retention: The frequency of documented low-dose high-frequency (LDHF) practice sessions per facility; and objective skills retention measured via Objective Structured Clinical Examinations (OSCEs) at 12-month intervals.

### 2.5. Outcome Measures

Outcome indicators, definitions, and data sources are summarized in Table 2. Primary outcomes are institutional maternal mortality, neonatal mortality within 24 h of birth, intrapartum stillbirth, and PPH incidence. Secondary outcomes include process indicators (e.g., uterotonic coverage for AMTSL, proportion of obstetric admissions receiving triage ultrasound) and intermediate clinical indicators (e.g., proportion of sick newborns initiated on bCPAP, SCBU survival).

### 2.6. Data Collection

Data collection is stratified by outcome type:Clinical Data (See Table 2): Quantitative will be collected from existing Ministry of Health (DHIS2) systems and project-specific sources. Project data collectors will collaborate with medical record officers to extract granular clinical data from consecutive maternity and newborn registers across all nine facilities. A preliminary review for validation and missing entries will be followed by cross-verification. Outcomes observed during the implementation and sustainability periods will be compared with retrospective baseline data collected three months prior to training.Implementation and Educational Data (See Table 3): Quantitative implementation metrics, including training logs and low-dose high-frequency (LDHF) practice frequencies, will be extracted from facility-level project registers. Educational indicators, such as performance on objective structured clinical examinations (OSCEs) and skills retention at 12 months, will be collected and tabulated by the mentorship teams.Qualitative data: Qualitative insights regarding implementation barriers and skill retention will be obtained from selected facility staff interviews, debriefs, and surveys.

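### OSCE skills retention is gathered by the mentorship teams who train and supervise the staff examined, with no independent check described, so it is open to bias in the programme's favour

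*Protocol article*

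**What the plan says.** Section 2.6 (Data Collection) assigns the educational indicators, namely OSCE performance and skills retention at 12 months, to the mentors: they "will be collected and tabulated by the mentorship teams". The other implementation metrics in the same paragraph, training logs and practice-session counts, "will be extracted from facility-level project registers".

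Section 2.3 gives the mentors' role in the intervention. The implementing organisation will supply "external mentors to cascade training and provide supportive supervision while observing patient care practices".

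Section 2.4.2 lists two measures under sustainability and retention: the frequency of documented practice sessions, and "objective skills retention measured via Objective Structured Clinical Examinations (OSCEs) at 12-month intervals". Table 2, the education and training table as printed, defines the retention indicator as "Percentage of trained staff maintaining competency at 12-month reassessment". Section 1.4 sets a matching programme objective, to "maintain high performance on knowledge and skills checks at 12-month intervals", and names mentoring as one of the means.

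For the clinical data, section 2.6 describes extraction by project data collectors working with medical record officers, then a review for validity and missing entries, then cross-verification. It describes no such step for the educational data. Section 3.5 (Limitations) covers the missing control group, the quality of historical registers and the inseparable effect of supplies. It does not mention who assesses skills.

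**The concern.** The people who deliver the training and supervision also produce the data on whether its effect on skills lasted. They have a stake in the answer, because good results on these checks are an objective of the programme and mentoring is one of the ways to reach it. Any leniency or selective recording would push the retention figure upwards and make decay in skills look smaller.

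The structured OSCE format limits subjectivity in the marking. It does not make the person who marks, or who compiles the marks, independent of the result. A reader who sees the measure called objective would probably assume some separation between trainer and assessor, and the article describes none.

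What is at stake is the credibility of one implementation outcome. The other sustainability measure in 2.4.2 counts activity, so it cannot show whether staff are still competent.

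**Working it through.** There is no figure in the plan to reproduce. The article gives no pass mark, expected pass rate, sample size or power for the OSCE outcome. The check has two parts.

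**1. The sections side by side**

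- Who delivers the training and supervision: external mentors (2.3).
- Who gathers and compiles the OSCE and retention results: the mentorship teams (2.6).
- What the results are used for: a sustainability outcome described as objective (2.4.2) and a programme objective (1.4).
- Checks on the clinical data: separate data collectors, validation, cross-verification (2.6).
- Checks on the OSCE data: none described in 2.6 or 3.5.
- Who scores the stations: not stated.
- Whether a mentor is tied to particular facilities: not stated.

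The overlap between delivering the intervention and handling its results is therefore a stated choice. The overlap between training and scoring is possible but not stated.

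**2. Possible size, if mentors score their own trainees**

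Let *p* be the true share of staff who are competent at 12 months, and *L* the share of non-competent staff who are passed. Both are assumptions; the article gives neither.

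Reported rate = *p* + (1 − *p*) × *L*

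| True *p* | *L* | Calculation | Reported | Excess |
|---|---|---|---|---|
| 0.70 | 0.10 | 0.70 + 0.30 × 0.10 | 0.73 | 3 points |
| 0.70 | 0.20 | 0.70 + 0.30 × 0.20 | 0.76 | 6 points |
| 0.80 | 0.10 | 0.80 + 0.20 × 0.10 | 0.82 | 2 points |
| 0.80 | 0.20 | 0.80 + 0.20 × 0.20 | 0.84 | 4 points |

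The reported rate runs from 73% to 84%, an excess of 2 to 6 points. The excess grows as true competency falls: with *p* = 0.50 and *L* = 0.20 the reported rate is 0.50 + 0.50 × 0.20 = 0.60, which is 10 points too high.

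The indicator in Table 2 is a level and not a change, so leniency that stays the same over time does not cancel out. Comparing two time points would be affected less. A true fall from 80% to 70% would be reported as 82% to 73% (9 points) at *L* = 0.10, and as 84% to 76% (8 points) at *L* = 0.20.

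**The case against.** The strongest reply is that section 2.6 speaks of data handling and not of examining. Leniency in scoring needs the mentor to be the examiner, and the article never says so. Naming OSCE examiners is also the kind of detail that a condensed article may leave to a fuller protocol or an assessment manual. This stands as a limit on the point: a reader might infer that mentors mark their own trainees, but the text does not establish it, and the 2-6 point figure depends on it. What the reply does not answer is that the article itself assigns collection and tabulation to the mentorship teams, calls the measure objective, and describes checks for the clinical data only.

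A second reply is that little depends on this outcome, and much of that stands. The primary review is of clinical effectiveness (2.1), whose data come by another route. The objective in 1.4 has no numerical threshold that a shift of a few points would cross. A reader might also take OSCE retention to be the main evidence for sustainability. The article does not support that: practice-session frequency stands beside it in 2.4.2, section 2.6 also seeks views on skill retention from staff interviews, debriefs and surveys, and section 3.6 rests sustainability on the handover to the ministry and on national trainers.

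A third reply is that exchanging mentors between facilities may be impossible if one team covers every site, since 2.3 does not attach mentors to facilities. That is fair. The remedy should depend on who trained and mentored the examinee, not on site.

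**Conclusion.** The point holds as a minor weakness in a stated design choice. The mentorship teams deliver the training and supervision and also gather and compile the only direct competence measure of the two sustainability outcomes in 2.4.2, with no check described like the one for clinical data. The measure is open to bias in the programme's favour. That is a risk, and nothing in the article shows that bias will occur.

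The size cannot be obtained from the document. If mentors score their own trainees, true competency is 70-80% and 10-20% of non-competent staff are passed, the reported rate would be 73-84%, an excess of 2 to 6 points. All three conditions are assumptions.

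The point does not reach the mortality and haemorrhage outcomes, which section 2.6 has extracted by other staff, or the practice-session counts, which come from project registers.

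**What to change.** In section 2.6, state three things:

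- Each 12-month OSCE is scored on the standard checklist by a member of the mentorship teams who did not train or mentor the examinee, for example one who mainly covers another site.
- Score sheets go directly to the project data collectors already named in that section, who tabulate them.
- Where no such scorer is available, this is reported as a limitation.

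The change needs no new staff. It costs rescheduling, plus some travel for the Bo site; the other eight of the nine facilities are in the Greater Freetown area (2.2). It would reduce the bias without removing it, because the scorers would still belong to the implementing organisation. How far it would lower the share of wrongly passed staff cannot be estimated from the article.
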